##### Cognitive status

The Montreal Cognitive Assessment [34], a widely used, cognitive test with high test-retest reliability (*r* = 0.92), has a better ability to detect mild cognitive impairment than the Mini-mental Status Exam [35]. Scores on the test vary from 0–30, where scores of 26 or above are considered normal.

##### Functional status

The activity-limitation domain of the Late Life Functioning and Disability Measure-Computer Assisted Testing (Version 1.04) (LLFDI-CAT) [36] will be used to measure the participant’s self-perceived, physical function. Drawing from a bank of 141 items, CAT continues until a standard error of 3 or less is obtained for the domain score, or a maximum of 10 items has been administered. The activity-limitation domain demonstrated high test-retest reliability (*r* = 0.85) among a sample of 102 community-dwelling older adults; it was moderately correlated (*r* = 0.72) with the physical component summary score of the Veteran’s Rand-36 [37]. The activity-limitation domain has two sub-scales: (1) basic mobility and handling and (2) daily activities. Standardized scores vary from 0 to 100, where the mean score is 50 and lower scores are indicative of greater limitation.

##### Hearing

We will use the Hearing Handicap Inventory for the Elderly Screening Version to measure hearing disability [38]. It is a 10-item self-report questionnaire. Scores vary from 0 to 40, and scores above 26 suggest an important hearing handicap. Its psychometric properties have been demonstrated across multiple studies [39].

##### Scooter characteristics

We will collect detailed information about the participant’s scooters including the number of wheels, smallest turning radius, size of wheels, length, width, and clearance.

##### Scooter physical accessibility of participant home and community

This will be measured by using 14 dichotomous (yes/no) questions, where no is scored as a 0 and yes is scored as a 1. Questions were derived in part from those asked in a study about environmental accessibility factors related to wheelchair use [40] and the Usability Scale for Assistive Technology-Wheeled Mobility version [41]. Higher scores indicate greater accessibility, which may facilitate increased mobility and social participation.

##### Visual attention and task switching

Trail Making B [42] will be used to measure visual attention and task switching. For this measure, the time required to draw lines between a sequential pattern of numbers and letters is recorded. The measure demonstrates high test-retest reliability (r = 0.95) [43]. Scores on the measure are predictive of on-road automobile driving performance [43].

##### Visual acuity

The Snellen eye chart [44] will be used to measure visual acuity. We will convert Snellen scores to the Logarithm of the Minimum Angle of Resolution (LogMAR) by taking the negative log of the Snellen score in decimal form [45], as LogMAR is recommended for statistical analyses [46]. LogMAR is based on a logarithmic scale (from 0 to 1), where 1 is indicative of perfect vision.

### Qualitative methods

Interviews will be conducted (1) at baseline prior to scooter training, (2) at 6 weeks, (3) at 6 months, and (4) at the end of the study. The initial interviews will focus on how participants currently use their scooters and the concerns they have, the second interviews will focus on how the intervention was experienced, and the final interviews will focus on longer-term outcomes of scooter use. We will interview the first ten interested participants in each group. Additional participants will be selected purposefully, depending on the analysis of the data from these first participants. These participants will be selected to elucidate themes emerging from the data from the first participants, and to understand negative cases better. For example, if one participant reacts negatively to the intervention, we will interview additional participants with similar demographic profiles.

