**Methods:**

This feasibility study will use a mixed-methods, rater-blinded, randomized control trial, with a two-step wedge design. The study has two arms: an immediate intervention group, which will receive the intervention directly after baseline assessments, and a delayed intervention group, which will receive the intervention after a 6-week period. Forty participants, who will be stratified based on whether or not participants have previously held a driver’s license, will be randomly assigned to each arm. The intervention for this study consists of 6 weeks of one-to-one scooter training by an experienced occupational therapist, who will provide training once or twice per week over the 6 weeks. The primary outcome measure is subjective scooter skills, measured using the Wheelchair Skills Test for scooters. Secondary outcomes include objective scooter skills, confidence, mobility, and satisfaction with selected participation activities. Descriptive measures include cognitive status, functional status, hearing, vision, physical accessibility of the home and community, and visual attention and task switching. Qualitative interviews will be conducted with the first ten willing participants from each group to learn about their scooter use and experiences with SCOOT.

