## Methods

### Study design

To conduct this exploratory, mixed-method, rater-blinded RCT, a two-step wedge design will be used, as illustrated in Fig. 1. With a step-wedge design, participants are randomly assigned to receive the same intervention at different times [22]. For this study, a total of 40 participants, stratified based on whether or not they have previously held an automobile driver’s license, will be randomly assigned to either the immediate intervention group or the delayed intervention group. As illustrated in Fig. 1, the immediate intervention group will receive the intervention after consent and baseline data have been collected, while the delayed group will receive the intervention after a 6-week delay. The primary endpoint of this study is at 6 weeks, so we can compare the effects of the intervention with the group who has yet to receive it.

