### Procedure

The research coordinator and principal investigator will train raters to administer all study measures. This training will include review of manuals, observations of pre-recorded mock interviews and assessments with practice scoring, practice administration with other research staff with feedback provided, and video recording of practice administration for self-reflection.

Upon enrolment, participants will be provided with a unique ID number, and the researcher will obtain written consent prior to baseline testing with all participants. The immediate intervention group will receive SCOOT after their baseline testing once or twice per week over a 6-week period (varying from 9 to 18 hours total), while the delayed intervention group will receive SCOOT 6 weeks after baseline testing. Upon completion of the intervention, all participants will be re-assessed at 6, 12, 26, and 52 weeks after randomization. Participants will also be asked not to participate in any additional training until 12 weeks have elapsed. The intervention will be discontinued upon the participant’s request, or if they are unable to continue with the research due to unforeseen events (e.g., illness).

Measures will be administered in a random order to reduce order effects. All measures, except the Wheelchair Outcome Measure (WhOM), will be collected by a blinded research assistant. The WhOM will be administered by the study therapist as this will inform the intervention. During training sessions, the therapist delivering the intervention will record any adverse effects of the intervention such as falls. As suggested by Little et al. [24], to reduce missing data, we will stress, during the consent process and whenever there is contact between participants and study personnel, the importance of collecting measurement data for the duration of the study, especially for those who discontinue the intervention.

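### The interview on how training was experienced is set at 6 weeks for both groups, before the delayed group has begun training

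*Protocol article*

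**What the plan says.** All references are to the protocol article.

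- **Qualitative methods** sets the interview times: "Interviews will be conducted (1) at baseline prior to scooter training, (2) at 6 weeks, (3) at 6 months", with a fourth at the end of the study. The second round has its own topic: "the second interviews will focus on how the intervention was experienced". The final interviews are given to longer-term outcomes. The calendar is not split by arm, and the sample comes from both: "We will interview the first ten interested participants in each group".
- **Abstract (Methods)** describes the same sample and purpose: "Qualitative interviews will be conducted with the first ten willing participants from each group to learn about their scooter use and experiences with SCOOT".
- **Procedure** fixes the start of training in the delayed arm: "the delayed intervention group will receive SCOOT 6 weeks after baseline testing". The course lasts 6 weeks. The same section says: "Upon completion of the intervention, all participants will be re-assessed at 6, 12, 26, and 52 weeks after randomization".
- **Study design** explains that the primary endpoint is at 6 weeks "so we can compare the effects of the intervention with the group who has yet to receive it".
- **Qualitative objectives** makes recipients' experience of the intervention a stated aim.

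**The concern.** The interview calendar fits the immediate group, whose course ends at week 6. It does not fit the delayed group, which at that time has had no session. Asked as planned, those participants have nothing to report on the topic assigned to that interview, and no interview is placed where their own course ends.

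What is at stake is the qualitative objective. The abstract promises accounts of the programme from each group, and the Analysis section uses qualitative data to supplement the fidelity and adherence figures. Qualitative methods also lets an adverse account prompt further sampling: "if one participant reacts negatively to the intervention, we will interview additional participants with similar demographic profiles". In the delayed group that step could start late if the first scheduled opportunity to describe training is months after it ended.

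**Working it through.** This is a timeline check. The plan states no figure of its own to reproduce.

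**Inputs**
- Training starts at week 0 (immediate) or week 6 (delayed) and lasts 6 weeks: Study design, Procedure.
- Interviews are at baseline, 6 weeks, 6 months and end of study: Qualitative methods.
- There are ten initial interviewees per group: Qualitative methods.
- Assessments are at weeks 6, 12, 26 and 52: Procedure.

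**Assumptions.** Six months is taken as week 26, and end of study as week 52, the last assessment. Training is counted from baseline testing and visits from randomization. The article gives no interval between the two, so none is assumed.

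**End of training** = start + 6 weeks.
- Immediate: 0 + 6 = week 6.
- Delayed: 6 + 6 = week 12.

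**Time from end of training to each interview** = interview week − end week.

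| Interview | Immediate | Delayed |
|---|---|---|
| Second, week 6 | 6 − 6 = 0 weeks | 6 − 12 = −6 weeks (course not begun) |
| Third, week 26 | 26 − 6 = 20 weeks | 26 − 12 = 14 weeks |
| Fourth, week 52 | 52 − 6 = 46 weeks | 52 − 12 = 40 weeks |

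So the second interview is at the end of training in one group and at its start in the other. The delayed group's first interview after training comes 14 weeks after the course ends.

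**How many interviews are affected**
- Initial interviewees: 10 + 10 = 20, of whom 10/20 = 50% are in the delayed group.
- Planned interviews: 20 × 4 = 80. The misplaced ones are the 10 delayed-group second interviews, 10/80 = 12.5%.
- Additional, purposively chosen participants are not counted, because their number is not given.

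**The Procedure wording.** The sentence on re-assessment puts every visit, including week 6, after completion of the intervention for all participants. At week 6 this is true only of the immediate group. The preceding text in the same section, and Study design, make the intended order clear.

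**The case against.** The strongest reply is that Qualitative methods names no time origin. Its first interview is placed relative to training, the course lasts six weeks, and the second topic is phrased in the past tense. Six weeks from the start of training is therefore a possible reading, and under it each group is interviewed as its course ends. Fig. 1 abbreviates the two arms separately and may show such an offset, but it is not available here. This reading cannot be excluded, but the section does not state it. Elsewhere the article counts from baseline or randomization, and Study design places its 6-week endpoint at the time when the delayed group is untrained. If the offset was intended, a short clarification is still needed.

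Other parts of the reply stand and limit the point:
- An interview's focus is not exclusive. The delayed group has two later interviews, and nothing forbids asking about training then.
- Fidelity and adherence rest on the percentages of skills taught and sessions attended; interviews only supplement them.
- The immediate group's ten interviews at the end of training still serve the objective.

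A reader might also infer that differing recall intervals bias a comparison of accounts between arms. The document does not support that: the qualitative analysis develops codes within and across participants and plans no contrast by arm.

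**Conclusion.** The point holds and is minor. As written, the calendar asks up to half of the initial interviewees (10 of 20) about training they have not received, and leaves about 14 weeks between the end of their course and their next interview. This weakens the qualitative objective in the delayed group. The conclusion rests on reading the 6-week interview as 6 weeks from baseline or randomization, and on taking 6 months as week 26.

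Two stronger readings should be resisted. One is that the trial as a whole treats week 6 as post-training in both arms. It does not: Study design correctly treats the delayed group as untrained then, and the conflict is confined to the interview calendar and one loose clause in Procedure. The other is that the primary comparison is compromised or that controls are trained early. Nothing in the article shows this.

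**What to change.** In Qualitative methods, set the second interview at completion of training in each group: week 6 for the immediate group, week 12 for the delayed group. Interview timing that differs by group reveals allocation, so the interviewer should not be the blinded rater.

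The cost is small. Ten interviews move to week 12, already an assessment time for all participants, so no visit or interview is added and the total stays at 80. The downside is that the delayed group then gives no week-6 account of scooter use without training. If that account is wanted, keep the week-6 interview with that different focus and add one at week 12, giving 80 + 10 = 90 interviews.

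As a minor wording correction in Procedure, remove the clause placing the week-6 visit after completion of the intervention, since it is true only of the immediate group.

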### Analysis

#### Quantitative data

Data will be input into a password protected document and will be double checked for accuracy. Descriptive statistics (e.g., means, frequencies, proportions, standard deviations) and distributions and box plots will be used to display all study data. The percentage of skills taught will be calculated to determine the treatment fidelity, and the percentage of sessions attended will be calculated to determine adherence. These quantitative data will be supplemented with data from the qualitative portion of the study. We will explore the use of multiple imputation for missing outcome measure data [47]. A detailed statistical analysis plan to handle various statistical analysis issues will be created [48]. To identify covariates that will be controlled for in the larger study, we will identify factors that are strongly related to the primary and secondary outcome measures. To determine the effect size for the primary and non-count secondary outcome measures, we will perform various models, controlling for baseline scores, using an intention-to-treat analysis. That is, all participants will be included in the group to which they were allocated for purposes of analysis, whether or not they completed the intervention for that group. As this is a feasibility study, we will also calculate effect sizes based on the intervention received (e.g., on an as-treated basis). Using G*Power 3.1.0, this sample size should give us the ability to detect a large effect size of 0.46 (with α = 0.05 and power = 80%). For count data (e.g., use, accidents, and falls), we will determine the effect size by using Poisson regression [49].

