### Randomization

The allocation of each participant will be communicated to the study research coordinator after baseline data and consent have been obtained. The allocations will be managed by the study statistician using an auditable computer program and a 1:1 allocation ratio within each stratum. Blocking sizes will not be revealed until needed for analysis.

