### Participants

For this feasibility study we plan to recruit 40 participants. As the majority of wheeled mobility users are older adults [4], the eligible community dwelling participants for this study are (1) English-speaking adults, (2) aged ≥ 60 years, (3) have one month or less combined experience of using a scooter within the past year, and (4) are able to independently transfer in and out of a scooter. We have not defined the population of interest based on their diagnoses (e.g., stroke, spinal cord injury, Parkinson’s disease), because the use of a scooter is not diagnosis specific. Individuals who have cognitive impairments that will prevent them from providing consent and from reliably completing the study questionnaires, reside in a nursing home, or plan to move outside the study intervention delivery area within the next year will be excluded.

Participants will be recruited through a variety of sources, including community healthcare units, vendors, and various seniors’ groups and seniors’ centres. Participants will be recruited through these organizations via posters, presentations, social media, and referrals. Occupational therapy staff and vendors will invite eligible clients to consider the trial.

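### The supplementary as-treated effect sizes are not a randomized comparison at 6 weeks, while a complier-average estimate from the same data would preserve one (minor)

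*Protocol article*

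**What the plan says.** The Quantitative data section of the Protocol article first plans effect sizes by intention-to-treat, controlling for baseline scores: "all participants will be included in the group to which they were allocated for purposes of analysis", whether or not they completed training. It then adds, on the ground that this is a feasibility study, that "we will also calculate effect sizes based on the intervention received (e.g., on an as-treated basis"). As-treated is the only received-treatment method named. The article does not say how much training counts as received.

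Four other places bear on this:

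- Study design: "The primary endpoint of this study is at 6 weeks", chosen so that the comparison is with a group not yet trained.
- Procedure: "The intervention will be discontinued upon the participant’s request, or if they are unable to continue with the research due to unforeseen events (e.g., illness"). Outcome data are still sought from people who stop training, and all participants are asked to take no additional training before week 12.
- Experimental intervention and Quantitative data: visits, hours of training and sessions attended are recorded.
- Background: estimates of the effect and its variance are among the aims of the study, which is meant to inform a larger trial.

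**The concern.** An as-treated analysis sorts people by what they received instead of by allocation. At 6 weeks only the immediate group has been offered SCOOT, so regrouping can go one way only: immediate-group participants counted as untrained join the delayed group. The people moved are self-selected or selected by events such as illness, and either could be related to a self-rated skill score. The trained group then loses its non-takers, while the comparison group keeps its own would-be non-takers and gains those of the other arm. A difference can appear even if SCOOT does nothing.

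What is at stake is the effect size that the feasibility study hands on. The article does not say which of its effect sizes will be used to plan the larger trial, and it does not warn that the as-treated figure lacks the protection of randomization.

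**Working it through.** **The plan's own figure.** The article gives no number for the as-treated analysis. The only figure in the section is the power statement, that the sample can "detect a large effect size of 0.46" at alpha 0.05 and 80% power. It serves here as a yardstick. With 40 participants in two groups, the detectable Cohen's f is 0.455 and power at f = 0.46 is 0.81, so the figure reproduces as f. On the d scale the detectable effect is 2 × 0.455 = 0.91 SD.

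**Inputs.**
- Sample: "For this feasibility study we plan to recruit 40 participants" (Participants) with "a 1:1 allocation ratio within each stratum" (Randomization), so about n = 20 per arm.
- p, the proportion who would take no training: not in the document. Assumed 1 of 20 (0.05) or 2 of 20 (0.10).
- g, the amount by which non-takers would score below takers without training, in SD: not in the document. Assumed 0.5 to 1.0. Where the analysis adjusts for baseline, g is the gap that remains after adjustment.
- τ, the effect of SCOOT in takers. No one in the delayed group is trained before week 6.

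**Bias of as-treated.** Set the untrained mean of takers to 0 and of non-takers to −g.
- Trained group: (1−p)n people with mean τ.
- Comparison group: pn non-takers from the immediate arm with mean −g, plus n delayed participants with mean −pg.
- Comparison mean = [p(−g) + (−pg)]/(1+p) = −2pg/(1+p).
- As-treated estimate = τ + 2pg/(1+p), so the bias is 2pg/(1+p).

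| Untrained in immediate arm | g = 0.5 | g = 1.0 |
|---|---|---|
| 1 of 20 | 2(0.05)(0.5)/1.05 = 0.05 | 2(0.05)(1.0)/1.05 = 0.10 |
| 2 of 20 | 2(0.10)(0.5)/1.10 = 0.09 | 2(0.10)(1.0)/1.10 = 0.18 |

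Against the detectable 0.91 SD, the extremes are 0.05/0.91 = 5% and 0.18/0.91 = 20%. If g = 0 the bias is zero; if non-takers would score higher, it changes sign.

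**Intention-to-treat and complier-average.**
- Intention-to-treat: the immediate mean is (1−p)τ − pg and the delayed mean is −pg, so the difference is (1−p)τ.
- Complier-average: (1−p)τ/(1−p) = τ. The gap g cancels because each arm keeps its own non-takers.

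**Illustration.** Take τ = 0.92, p = 0.10, g = 0.5.
- Large-sample values: intention-to-treat 0.83, as-treated 1.01, complier-average 0.92.
- Simulation with 20 per arm (20,000 runs): means 0.83, 1.01 and 0.91; SDs of the estimates 0.33, 0.32 and 0.36.

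**Effect on planning in that case.** Using n per arm ≈ 2(1.96 + 0.84)²/d² = 15.68/d², d = 0.83 needs 15.68/0.689 = 22.8, so 23 per arm, and d = 1.01 needs 15.68/1.020 = 15.4, so 16. A larger trial analysed by intention-to-treat with the same uptake would see the 0.83.

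**The case against.** The strongest reply is that the analysis is supplementary and as-treated is introduced only as an example. Intention-to-treat is defined in full and comes first. A detailed analysis plan is promised, and it could define receipt and choose another estimator. All of this stands, and it keeps the point minor. It does not remove it, because the one method that the article names is the non-randomized one. That is a stated choice and not a detail left out.

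Four stronger readings are tempting, and the document supports none of them.

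- **That the expected 80% adherence means 4 of 20 untrained.** This would give a bias of 0.17 to 0.33 SD. But adherence is defined as the percentage of sessions attended; it is not a share of people without training. The retention target does not supply p either, since people lost to follow-up have missing outcomes and are not regrouped.
- **That the bias runs upward.** Illness would push it that way. People who decline because they already feel capable would push it the other way.
- **That the discontinuation rule shows many people will be regrouped.** That depends on what counts as received. If one session is enough, people who start and then stop are receivers and never move. If nobody attends no session at all, as-treated equals intention-to-treat.
- **That the as-treated figure will be used to size the larger trial.** The article does not say so.

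It is also fair to say that the bias in the table is below the sampling SD of about 0.32 at this sample size. It is systematic, however, and a larger sample would not shrink it. Finally, the complier-average estimate has a price: it needs an assumption of its own and adds essentially no new test.

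**Conclusion.** The point holds as a minor one. The named as-treated method gives up the randomized comparison at 6 weeks, and its estimate is off by 2pg/(1+p) SD. That is 0.05 to 0.10 SD with 1 of 20 untrained and 0.09 to 0.18 SD with 2 of 20, for an outcome gap of 0.5 to 1.0 SD.

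These sizes rest on assumed values of p and g, on no training in the delayed group before week 6, and on regrouped participants having had no effect from training. They are illustrations of scale and not predictions for this trial. The intention-to-treat estimate is unaffected. Allocation, session records and outcomes sought after discontinuation are all collected, so a received-treatment estimate that respects randomization is within reach.

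**What to change.** In the analysis plan:

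1. Keep intention-to-treat as the main estimate and name it as the one used to plan the larger trial.
2. For the received-treatment effect size at 6 weeks, use a complier-average effect with allocation as the instrument and adjustment for the baseline score (two-stage least squares).
3. Define received as at least one session in the therapist's record. State the exclusion restriction: allocation affects the outcome only through receipt. The low threshold makes this plausible; a stricter one would count partly trained people as untrained and violate it.
4. If an as-treated figure is still shown, label it non-randomized and do not use it for sample size.

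The cost is some wording and a few lines of code, with no new data. The confidence interval widens by about 1/uptake: 1/0.95 = 1.05 times with 1 of 20 untrained and 1/0.90 = 1.11 times with 2 of 20. The estimate gives essentially the same test as intention-to-treat, so its value lies in the size of the effect and not in added evidence.
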